### Specific experiments

**Placenta v. cord blood methylation profiles:** To the best of our knowledge, no study has compared the methylation profiles of the ~100 imprinted genes in placental tissue and cord blood. The outcomes of these comparisons will potentially shed light on the regulatory mechanisms and epigenetic profiles of adverse and healthy pregnancy outcomes.

**Cases v. controls methylation profiles:** The results of the placenta v. cord blood studies will help to determine which sample sets are compared in trying to identify the methylation profiles associated with adverse pregnancy and newborn outcomes. Comparisons will also be made between ethnic sub-groups. All the above experiments will be performed in duplicate with adequate quality control measures,

**Sample pooling for methylation profiles:** Pooling samples of 'healthy' controls to act as a reference standard for epigenetic studies has been proposed in the literature. Given that FGLS provides an ideal opportunity to use samples from newborns whose intra-uterine growth has been optimal, we plan to explore this possibility with FGLS samples drawn from the three INTERGROWTH-21st centres. This might involve pooling samples collected both within and across these centres, although the experiments would need to be performed in India if samples are collected there.

**Placental expression analyses:** We will follow the same experimental design outlined in the Movassagh et al. (2010) study. Quantitative real-time PCR will be performed for target genes, selected from the methylation studies, using validated Taqman Gene Expression Assay primers (Applied Biosystems, Foster City, CA) normalised against house-keeping gene data. In the long-term, we also plan to characterise global expression patterns in placental tissue using the new Illumina HT-12 v4 expression chip, for comparison between sub-groups and methylation profiles, as well as between normal and adverse pregnancy and newborn outcomes.

### **Nutritional status**

To supplement the epigenetic studies above, we will also assess the nutritional status of the 500 cases and 500 controls selected for the proof-of-concept study, by measuring:

- Micronutrients in maternal blood at booking and cord blood at delivery
- Putative markers of methyl donation, e.g. S-adenosylmethionine (SAM) to S-adenosylhomocysteine (SAH) ratio
- Neonatal body composition

The rationale for adding these measures is that they should facilitate the interpretation of the epigenetic data and the characterisation of specific sub-phenotypes, in particular IUGR and SGA.

**Micronutrient assays:** As with the epigenetic studies, there are a large number of technological platforms available to assay micronutrients and some controversy regarding the most appropriate ones to measure. The assessment of micronutrients in mother's blood is made even more complex by physiological alterations such as haemodilution and the hyperlipidaemic state of pregnancy.

We will therefore seek guidance from the Biomarker Group consisting of experts in the field before finalising the list of analytes and the methods to use. We will also draw heavily on the expertise of our collaborators at SMRU, Thailand who have considerable experience of assessing nutritional status in their populations. At present, based on unpublished data from their studies and our reading of the literature, the following analytes have been proposed as candidates to measure:

- Retinol Binding Protein (RBP)/Vitamin A
- Iodine (maternal) and TSH (newborn)
- Ferritin and Soluble Transferrin Receptor (sTfR) – markers of Fe deficiency
- Zinc protoporphyrin (ZnPP)
- Folate, thiamine, choline and zinc
- Vitamin D
- CRP and  $\alpha$ GP

In Thailand, we will also measure Dichloro-Diphenyl-Trichloroethane (DDT) metabolite levels as DDT was used as an insecticide for malaria control in Northern Thailand until it was replaced by Deltamethrin in 2000. However, high serum DDT residues, which affect serum retinol levels and probably thiamine as well, are still detected in pregnant women living in the Mae La camp. We also plan to ask the local investigators to identify other possible chemical exposures to measure. Final decisions about which exposures to measure and where the samples will be analysed will be made by the Biomarker Group; however, we will ideally use centralised facilities.

**Neonatal body composition:** As part of our Wellcome Trust/EPSCRC funded research program, we are already starting to measure neonatal body composition in: a) term normal birth weight, b) preterm and c) term IUGR/SGA infants enrolled in the UK component of FGLS and PPFS. To do so, we are using an infant-sized, air-displacement plethysmograph (PEA POD Infant Body Composition System, Life Measurement, Concord, CA, US). The study is being conducted so as to correlate fetal growth patterns with better measures than birth weight alone, i.e. the relative contributions of body fat, lean tissues and bone, all of which are key indicators of the adequacy of intra-uterine nutrition.

The PEA POD system compares well with the 4-compartment reference model, which is considered the best choice for assessing body composition in humans. In contrast, however, it is easy to perform; takes only a few minutes to complete; infant movement during the measurement is not a significant problem; the measurements can be repeated as frequently as needed, and the results are immediately available.

The system is now recognised as an established method to assess neonatal body composition in developed countries, and it is suggested that it may offer important insights into which fetal growth parameters most closely reflect the generalised nutritional state of neonates and infants. However, there are no published data about its use in resource-poor settings as, to the best of our knowledge, the system has been installed in only one site in such a setting, as part of a collaboration between Jimma University, Ethiopia, and the Department of Human Nutrition, University of Copenhagen.

We now propose installing PEA POD systems in four of the centres in resource-poor settings to give a much more detailed assessment of nutritional status and growth than birth weight and gestational age alone.

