### 1.11 Biological samples

#### Oxford FGLS extension (INTERBIO-21st Fetal & Infant Growth Study)

From 2011 to 2014, we will collect and store maternal blood (12ml) at booking, a urine sample (5ml) at each follow-up ultrasound appointment, as well as maternal faeces (5ml, only if the mother has opened her bowels) and cord blood (12ml)/placental (9x 5mg) samples at delivery (in addition to the pregnancy and fetal growth data) from a total of 1,000 pregnancies. The samples will be used for nutritional and epigenetic studies into fetal growth. The INTERBIO-21st Fetal & Infant Growth Study will continue to monitor fetal growth and the growth and development of the infants using the same protocols as the FGLS component of INTERGROWTH-21st <http://www.medscinet.net/intergrowth/protocol.aspx>

<http://www.medscinet.net/Interbio/protocol.aspx?lang=1> (See Appendix K).

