#### Oxford NCSS extension (INTERBIO-21st Neonatal & Infant Growth Study)

From 2011 to 2014, we will collect and store maternal blood (12ml) at delivery, as well as maternal faeces (5ml, only if the mother has opened her bowels) and cord blood (12ml)/placental (9x 5mg) samples at delivery (in addition to the pregnancy data) from a total of 10,000 pregnancies. The INTERBIO-21st Neonatal & Infant Growth Study will continue to monitor the growth and development of the infants using the same protocols as the NCSS component of INTERGROWTH-21st <http://www.medscinet.net/intergrowth/protocol.aspx>.

<http://www.medscinet.net/Interbio/protocol.aspx?lang=1> (See Appendix K).

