In all centres, we plan to collect and store maternal blood, maternal faeces and cord blood/placental samples at delivery (in addition to the pregnancy and fetal growth data) from a total of 2,500 pregnancies (500 per centre). For details of blood, faecal and tissue sample collection see the INTERBIO-21st Operations Manual.

Detailed information will also be acquired about gestational age and fetal growth patterns starting at <14 weeks' gestation. This is of great relevance because of the recent evidence that fetal growth discrepancies, which can be detected by ultrasound as early as the 1st trimester, are associated with increased risks of preterm birth, low birth weight, and SGA at birth .

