**Anthropometric measurements**

All babies, i.e. all cases and controls, born during the study period will have weight, length and head circumference taken within 24 hours of delivery.

Standardised, electronic, digital, newborn weighing scales with a precision of 10g will be used and their calibration status will be checked twice a week; they will be replaced if they are faulty and cannot be repaired. We shall also provide all clinics with standardised infantometers for length (precision 0.1 cm) and tape measures for head circumference (precision 0.1 cm); these will be similarly calibrated and maintained. All anthropometrists will be trained centrally and monitored during the study following standard procedures by the Anthropometric Standardisation Unit; they in turn will train the nurses/midwives in how to apply the study's measurement protocol.

For a small subgroup, the following additional anthropometric measurements will be taken: arm circumference; thigh circumference; abdominal circumference and skinfold thickness, as well as neonatal body composition using air displacement plethysmography (PEA POD) in some centres.

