### Sample size

This is a great challenge in any field-study of this magnitude and even more difficult when exploring risk factors with relatively unknown degrees of association and prevalence in the population. The key issue is to reach a balance between logistical demands, including the need to maintain data quality in these populations, and power calculations especially for the planned epigenetic studies. Having said that, our co-investigators, [name] and [name] in the Wellcome Trust Centre for Human Genetics, Oxford, have considerable experience of conducting candidate gene and genome-wide association studies (GWAS) in related fields and the lessons learned over the last 15 years will be pertinent to the proposed studies.

To illustrate the point, Cardon & Zondervan reviewed how the complex interplay between genotype, phenotype, environmental factors and sample size affects the ability to detect disease susceptibility variants in population-based association studies. They concluded that thousands of cases and controls are required to detect common variants with small effect sizes in such studies.

Three examples demonstrate the need to study large numbers to identify genes influencing quantitative traits involved in metabolic function, such as birth weight. Nearly 120,000 individuals were genotyped to identify three loci influencing anthropometric measures (waist circumference and waist-hip-ratio) of central obesity and fat distribution in a recently published meta-analysis of 16 GWAS, followed by large-scale replication testing. Using similar methodology (GWAS meta-analysis followed by replication), over 90,000 individuals were genotyped to confirm that two loci are associated with BMI and to identify six additional loci and, more recently, nearly 40,000 European individuals were genotyped in identifying variants in *ADCY5* and near *CCNI* associated with fetal growth and birth weight.

For the nested case-control studies, we are collecting samples from 2,000 controls; and 2,000 cases from pregnancies with adverse outcomes, e.g. delivery at <38+0 weeks' gestation, term IUGR/SGA. In addition, we have the potential to include 400 cases and 2100 controls from the FGLS population in the analysis, taking into consideration the possibility of selection bias in the selection of FGLS population controls.

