### General Objectives

The aim is to conduct a hypothesis-testing, proof-of-concept study comparing 500 normal birth weight and 500 term IUGR/SGA newborns (using both cord blood and placental samples) taken from the samples collected in the context of both the INTERBIO-21st Fetal and Newborn Studies. This will be the first in a series of experiments utilising samples collected for the INTERBIO-Bank.

We aim to assess DNA methylation patterns in ~100 imprinted genes previously implicated in fetal growth. Our hypothesis is that maternal micronutrient deficiency, particularly of folate and other methyl donor factors, results in impaired fetal growth, development and pregnancy outcomes, through altered DNA methylation.

We will therefore correlate these methylation patterns with pregnancy (clinical outcomes, fetal growth), nutritional (micronutrient assays), and neonatal (growth, development and body composition) data, which will allow us to:

1. Study the effects of environmental and nutritional factors on the epigenome;
2. Develop new phenotypic definitions of LBW and other adverse pregnancy outcomes

If validated, the results could inform knowledge-based actions to address underlying problems, such as poor nutrition and infection, leading to improved outcomes. The data will, in addition, serve to define normal variability in the epigenome and inform the design of future epigenome-wide studies, once the cost has fallen, as inevitably it will with technological advances.

In the long-term, we would also wish to correlate these epigenetic findings with single nucleotide polymorphism (SNP) genotyping data from a GWAS given the increasing evidence that epigenetic regulation is influenced by genetic factors and the recently published data implicating variants in *ADCY5* and near *CCNI* with fetal growth and birth weight.

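### Booking-blood micronutrients and neonatal body composition are promised for all 500 proof-of-concept cases and 500 controls, but about 71–80% of randomly drawn cases would come from a sub-study that enrols at delivery

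*Protocol*

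**What the plan says.** Appendix K, Programme II, 'Nutritional status': "we will also assess the nutritional status of the 500 cases and 500 controls selected for the proof-of-concept study, by measuring" three things, namely "Micronutrients in maternal blood at booking and cord blood at delivery", putative methyl-donation markers, and neonatal body composition. 'General Objectives' gives the reason: "Our hypothesis is that maternal micronutrient deficiency, particularly of folate and other methyl donor factors, results in impaired fetal growth", through altered DNA methylation.

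Programme II, 'Study design', defines the sample. The 500 term IUGR/SGA cases are selected at random from the INTERBIO-Bank. The 500 controls come either from the lowest-risk women in the Fetal Study or from all normal outcomes, with the choice left to the Steering Committee. 'General Objectives' confirms that the samples come from both the Fetal and the Neonatal Studies.

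Maternal blood timing depends on the sub-study:
- Oxford Fetal extension (section 1.11): "we will collect and store maternal blood (12ml) at booking".
- Oxford Neonatal extension (section 1.11): "we will collect and store maternal blood (12ml) at delivery, as well as maternal faeces". Appendix K likewise has Neonatal Study samples taken at birth, and 'Selection of Cases and Controls' has mothers screened on admission for delivery.
- Fetal Study in Appendix K: "we plan to collect and store maternal blood, maternal faeces and cord blood/placental samples at delivery".

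On body composition, 'Anthropometric measurements' in the Neonatal Study lists additional measures for a small subgroup, "as well as neonatal body composition using air displacement plethysmography (PEA POD) in some centres". 'Neonatal body composition' in Programme II proposes PEA POD systems in four resource-poor centres, besides the UK measurements already starting.

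**The concern.** A study cannot hold its own booking blood from a woman it first meets in labour. If most of the 500 cases are such women, the booking measurement promised for all of them does not exist for most of them, and no analysis plan can create it later. The same applies to body composition: it must be measured around birth and cannot be added once stored samples have been selected.

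Booking blood is the only listed maternal-blood measure taken before most fetal growth has happened, so its absence weakens the exposure side of the stated hypothesis. There is also a route to bias. If controls are taken from the lowest-risk Fetal Study women, and that study draws blood at booking, controls would have booking values while most cases would not, so availability would follow case status. Filling the gap with delivery values would then tie sampling time to case status.

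**Working it through.** **Inputs**
- Neonatal Study IUGR/SGA cases: 200 per site ('Operational definition of cases and controls'). Five centres give 5 × 200 = 1,000, matching the 1,000 term IUGR/SGA newborns in 'Sample size for epigenetic studies'. Similarly, 5 × 400 = 2,000 matches the 2,000 cases in 'Sample size'.
- Fetal Study size: 2,500 pregnancies at 500 per centre, i.e. five centres ('INTERBIO-Bank study design').
- Cases from the longitudinal cohort: "we have the potential to include 400 cases and 2100 controls from the FGLS population". Since 400 + 2,100 = 2,500, this appears to be the Fetal Study. The 400 mixes case types, so it is an upper bound for IUGR/SGA.
- IUGR/SGA rate: expected to be below 10–15% ('Definitions of cases and controls for the data analyses').

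**Expected Fetal Study cases in a random 500**

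With F the number of Fetal Study IUGR/SGA cases, the expected number is 500 × F/(F + 1,000).

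| Assumption | F | Share | Of 500 | Left from Neonatal Study |
|---|---|---|---|---|
| 10% of 2,500 | 250 | 250/1,250 = 20.0% | 100 | 400 (80%) |
| 15% of 2,500 | 375 | 375/1,375 = 27.3% | 136 | 364 (73%) |
| All 400 are IUGR/SGA | 400 | 400/1,400 = 28.6% | 143 | 357 (71%) |

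A rate below 10% lowers the Fetal Study share: at 5%, 125/1,125 = 11.1%, about 56 cases. For a given rate the share is the same with three, five or seven centres, because both sub-studies scale per centre. These are expected counts, not guaranteed maxima.

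**Allowing for Oxford's discarded first-trimester samples**

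Section 1.11 stores these and links them to INTERBIO data. Assuming they served all 200 Oxford Neonatal cases:
- F = 250: (250 + 200)/1,250 = 36.0%, i.e. 180 of 500.
- F = 400: (400 + 200)/1,400 = 42.9%, i.e. 214 of 500.

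That still leaves 286–320 of 500 (57–64%) with no early-pregnancy maternal sample.

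**The plan's own sample-size figure**

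Table 1 gives 342 cases for 0.20 v. 0.35, alpha 5.0 × 10⁻⁴, 80% power, 1:1. A two-sided two-proportion calculation with continuity correction gives 343, so it reproduces. It sizes the methylation comparison, which uses cord blood and placenta and keeps its 500 v. 500.

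The protocol gives no effect size for micronutrients. Borrowing the Table 1 scenario only as a measure of scale (no continuity correction), power is 97% with 500 v. 500, 13–26% with 100–143 pairs, and 43–59% with 100–143 cases against 500 controls.

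**Body composition**

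The promise covers all 1,000 infants. The Neonatal Study, the source of most cases, plans it for a small subgroup in some centres. The proposed four installations plus the UK could equip five centres, but nothing extends the measurement to every infant there.

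**The case against.** The strongest reply is that little of substance is lost. The hypothesis refers to maternal deficiency without specifying booking. Cord-blood micronutrients are in the same list, and delivery maternal blood is stored for Neonatal Study women. The nutritional measures are introduced as a supplement to the epigenetic work, the only part that Table 1 sizes. Analytes, methods and the control source are openly provisional. All of that stands, and it limits the point: a reader might infer that the hypothesis cannot be tested in this sample, and the documents do not support that. A weaker test remains, with exposure measured at birth.

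Three other tempting readings also go too far.
- That taking every Fetal Study case could not reach 500. This depends on five centres; seven likely sites are listed, and 15% of 7 × 500 = 3,500 is 525.
- That section 1.11 and Appendix K flatly contradict each other on Fetal Study blood. In the Appendix K sentence the timing phrase may govern only the cord and placental samples. Figure 3, on collection periods, is not shown, and the Operations Manual is not at hand.
- That body composition is confined to a few centres. The proposed PEA POD installations could cover most or all of them.

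The bias argument is conditional too: no passage proposes substituting delivery for booking blood, and the control source is undecided. None of this supplies study booking blood for women enrolled at delivery, nor does it square a small subgroup with all 1,000 infants.

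**Conclusion.** Wrong as written. The nutritional assessment promised for 500 cases and 500 controls does not fit the sample defined under 'Study design'. About 71–80% of cases (357–400) are expected to have no study booking blood, and body composition is not planned for all infants. The loss is confined to the booking-exposure comparison at its stated size and to complete body-composition data; the methylation comparison and the growth standards are unaffected.

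The size rests on a random draw across both sub-studies, 1,000 Neonatal term IUGR/SGA cases, 250–400 from the Fetal Study, and every Fetal Study woman having booking blood. If booking collection is confined to Oxford, fewer cases would have it. The link with case status arises only if controls come from the lowest-risk Fetal Study women.

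**What to change.** Amend Appendix K, Programme II, before samples are selected:
1. Limit the booking-micronutrient comparison to cases and controls who both have a booking sample, and restate its expected size (about 100–143 cases under the present draw, or a new figure if cases are selected on having such a sample).
2. For the full 500 v. 500, name cord blood as the micronutrient source, with delivery maternal blood where it is stored in both groups. State that booking and delivery values will not be pooled, and that delivery values reflect status after growth has occurred.
3. Describe body composition as a sub-analysis of infants measured in PEA POD centres, and reconcile 'Anthropometric measurements', 'Nutritional status' and 'Neonatal body composition'.
4. State whether Fetal Study maternal blood is drawn at booking, at delivery or both, so that section 1.11 and 'INTERBIO-Bank study design' read alike.
5. If Oxford's discarded first-trimester samples are to count as booking samples, say so.

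The cost is protocol wording and a smaller stated size for one supplementary analysis. No extra samples, visits or staff are needed.

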### **Sample size for epigenetic studies**

As discussed on page 18, it is extremely difficult to provide reliable power calculations at the moment for epigenetic studies: the field is too new and very few relevant studies have been conducted, especially in humans, to enable power calculations to be performed. It is also unclear at present to what extent it will be necessary to map DNA methylation at high resolution across the entire genome, which will inevitably influence the epigenotyping strategy and choice of platform, e.g. bisulfite sequencing or array-based technology. However, having said that, the sample size chosen matches that in the NIH National Standard for Normal Fetal Growth Study and we feel comfortable that it provides a reasonable compromise between cost, expediency and logistical demands.

The estimated samples sizes required to detect the effects of methylation status on adverse pregnancy outcomes are inevitably based on a range of assumptions, since the spectrum of methylation changes and their corresponding effect sizes are unknown. Table 1 shows the sample sizes required to detect differential methylation in cases vs. controls. The following assumptions are made:

- Methylation status is either on/off, and so the proportion of cases vs. controls with methylated status is analysed.
- Methylation proportion among controls of 0.2, with proportion in cases varying from 0.3-0.5, corresponds to an odds ratios (OR) of the effect of methylation status on outcome from 1.7-4.0.
- A significance threshold  $\alpha$  of  $5.0 \times 10^{-4}$  (Bonferroni-corrected threshold for 100 candidate imprinted genes) vs.  $5.0 \times 10^{-7}$  (commonly applied genome-wide significance threshold in GWA studies).
- Power of 80% vs. 90%
- Case: control ratio either 1:1 or 1:3

